**Primary outcomes**			
1. Time taken for alleviation of symptoms	Earlier symptom resolution	Yes/No	Multivariant analysis, cox proportional hazards models
2. Time taken for viral load clearance	Earlier RT-PCR negative	Positive/ negative	
3. HRCT chest score at day 4	Better score resolution	Score from 0 to 25	Mixed Ordinal Logistic Regression Model

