### Outcomes {12}

Primary outcomes will include time to SARS-CoV-2 RT-PCR clearance, alleviation of symptoms, and better high-resolution computerized tomography (HRCT) chest score. Thirty-day mortality will be used as a secondary outcome. SARS-CoV-2 RT-PCR will be done on admission day (0 day) and then after every 4th day for 12 days or till the symptoms are resolved and RT-PCR gets negative. Symptom resolution is defined by the resumption of mild to moderate symptoms COVID-19 symptoms (defined by the definition of symptoms). RT-PCR will only be shown as positive or negative (as a limitation of our study of not getting the viral load). Time taken for the alleviation of symptoms will be measured as the number of days the patient remained symptomatic, i.e., the difference between onset of COVID-19 symptoms to complete resolution. HRCT chest scoring will be done as follows: Lungs divided into five lobes and each lobe is scored as 0 (no involvement), 1 (< 5% involvement), 2 (up to 25% involvement), 3 (26–49% involvement), 4 (50–75% involvement), and 5 (> 75% involvement). The overall HRCT chest score will be from 0 (no involvement) to 25 (maximum involvement) [16]. The HRCT findings are described via standard international terms, which are classified by the Fleischner Society glossary with peer-reviewed literature on viral pneumonia. The terms being used are ground glass opacity (GGO), crazy-paving pattern, and consolidation [17, 18]. Like a previous study [19], a maximum of 4 HRCT chest will be performed starting from day 0 followed by every fourth day till patients’ PCR become negative.

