## Data collection and management

### Plans for assessment and collection of outcomes {18a}

Microsoft Access, a database management system (DBMS) of Microsoft Office, will be used to ensure the data safety. SARS-CoV-2 RT-PCR test and HRCT score will be done every fourth day while COVID-19 symptoms evaluation will be done on daily basis to access the time taken for the alleviation of symptoms. Thirty-day mortality will be assessed by the number of deaths per group after 30 days of randomization in all groups. All trial data will be collected by site investigators and two site investigators will enter the data, recheck twice for possible errors separately, and make certain its integrity. Pre-approved questioner regarding demographics of the patient and data collection will be used while all the testing will be done by International Organization for Standardization (ISO) certified laboratory (Shaukat Khanum Laboratory). Principal investigators will visit twice weekly the study site. Trial steering committee members will make unexpected and unplanned visits as well. There is no conflict of financial and non-financial interest with sponsors and researchers.

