### Plans to promote participant retention and complete follow-up {18b}

All the participants will be ensured their safety and will be guided about the study conduction and its beneficial outcomes. This study will be conducted till the patients hospitalized or home-quarantined in homes test negative for SARS-CoV-2 RNA in two consecutive nasopharyngeal swabs done using RT-PCR. All the data will be collected while the patient is already admitted in the hospital except 30-day mortality. Contact numbers and addresses of all participants will be reported at the start of study for which can be used, if needed, after written consent is obtained from the patient. Follow-up will be done using phone numbers of the patients to access the mortality benefit of intervention.

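### The HRCT primary outcome is fixed at day 4 but paired with a mixed model and scans that stop on PCR negativity; the scans analysed must be settled, because later ones can bias the comparison

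*Protocol article*

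**What the plan says.** Four places in the protocol article bear on the HRCT endpoint.

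- **Table 1, primary outcome 3:** the outcome is "HRCT chest score at day 4" and the method is "Mixed Ordinal Logistic Regression Model". The hypothesis column speaks of the score resolving better, which hints at change over time. The table does not state which scans enter the model, what the random effect is for, or which covariates are used.
- **Outcomes {12}:** the primary outcome is a "better high-resolution computerized tomography (HRCT) chest score", with no day attached. On scheduling: "a maximum of 4 HRCT chest will be performed starting from day 0 followed by every fourth day till patients’ PCR become negative".
- **Plans for assessment and collection of outcomes {18a}:** "SARS-CoV-2 RT-PCR test and HRCT score will be done every fourth day", with no stopping rule for scans.
- **Plans to promote participant retention and complete follow-up {18b}:** the study continues until patients "test negative for SARS-CoV-2 RNA in two consecutive nasopharyngeal swabs done using RT-PCR", a different end point from the single PCR condition in {12}.

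Table 1 also lists time to PCR clearance as a primary outcome, expected to come sooner on iodine. Section {20b} leaves adjusted analyses optional. Section {20c} offers a sensitivity analysis for missing data and imputation for patients who withdraw consent; it does not mention scans omitted because PCR turned negative.

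**The concern.** The stated outcome, model and schedule do not fit together. One score per patient at one day needs no patient-level random effect, so a mixed model points to repeated scans. The repeated scans are cut off by another primary outcome. If iodine clears virus faster, as hypothesised, fewer iodine patients are scanned on days 8 and 12, and those still scanned are the slow clearers. If slow clearance goes with worse lungs, the later scans of a faster-clearing arm come from a sicker selection than those of placebo. A real radiological benefit could be hidden, or a harm suggested where there is none.

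There is a smaller exposure at day 4. The stopping clause does not say whether a patient who first tests negative on day 4 still has that day's scan. If not, the named endpoint would also lose patients selectively.

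**Working it through.** **1. Schedule.** Outcomes {12} gives PCR timing as "SARS-CoV-2 RT-PCR will be done on admission day (0 day) and then after every 4th day for 12 days". Applied to HRCT, days 0, 4, 8 and 12 make 4 scans, which matches the stated maximum. Section {18a} puts PCR and HRCT on the same rhythm.

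**2. Day 4.** Recruits are diagnosed patients, so PCR is expected to be positive at day 0 (not stated in so many words). The first possible negative is then on day 4, the day of the scan. If scan and swab are done together, a day-4 negative cancels only days 8 and 12, and the day-4 score exists for everyone still in follow-up.

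**3. Days 8 and 12.** If one negative PCR ends scanning, no day-8 score is ever seen in a patient who was negative at day 4. A model using later scans must extrapolate to those patients, and the trial's data cannot test the extrapolation.

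**4. Size, by simulation.** The article gives no clearance rates, HRCT standard deviation or correlations, so every input is an assumption: 200,000 patients per arm; no true HRCT effect; between-patient SD 3, slope SD 1.5 per visit, residual SD 1.5; treatment log-odds on clearance 0 or 0.8; strength of the link between PCR and HRCT 0 to 1.5. A linear score stands in for the ordinal one. Entries are treatment minus control in score points, day 8 / day 12; positive means treatment looks worse.

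| Scenario | Unstructured model | Random intercept only | Observed scans only |
|---|---|---|---|
| Treatment does not change clearance | about 0 | about 0 | about 0 (at most 0.04 in size, any model) |
| Faster clearance, unrelated to HRCT | about 0 | about 0 | about 0 |
| Faster clearance, stopping follows observed HRCT scores | within 0.03 | 0.10–0.19 / 0.33–0.50 | 0.33–0.55 / 0.74–1.08 |
| Faster clearance, stopping follows the unobserved HRCT course | 0.13–0.25 / 0.28–0.50 | 0.21–0.36 / 0.58–0.82 | 0.27–0.46 / 0.71–1.02 |

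At day 4 the difference was 0.00 in every scenario. In the last row, 31–36% of control and 14–22% of treated patients were still scanned at day 12. With 50 per arm that is about 16–18 against 7–11 patients (0.31 × 50 = 15.5, 0.36 × 50 = 18; 0.14 × 50 = 7, 0.22 × 50 = 11).

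**5. Value of the day-0 score.** The 50 per arm in Sample size {14} is declared arbitrary, so there is no calculation to reproduce. For one pairwise comparison at 80% power and alpha 0.05 (two-sided assumed; sidedness is not stated):

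- Unadjusted: (1.960 + 0.842) × √(2/50) = 2.802 × 0.200 = 0.56 SD.
- Linear ANCOVA multiplies the SE by √(1 − r²), with r the assumed day-0/day-4 correlation.
- r = 0.5: √0.75 = 0.866, SE down 13%, detectable difference 0.49 SD.
- r = 0.7: √0.51 = 0.714, SE down 29%, 0.40 SD.
- r = 0.8: √0.36 = 0.600, SE down 40%, 0.34 SD.

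These cuts do not carry over to the SE of a proportional-odds log odds ratio. A small null simulation (50 per arm, 30 replicates per setting) gave mean SEs of 0.353 unadjusted against 0.360 adjusted at r = 0.5, and 0.353 against 0.371 at r = 0.8. There the gain comes as power, because the adjusted log odds ratio is larger.

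**The case against.** The strongest reply is that Table 1 already names day 4, and that day is safe when scan and swab coincide. A mixed model can also be coherent without the later scans: it could use the day-0 and day-4 scores as repeated measures, or carry a random effect for the three sites. Even with later scans, a correctly specified likelihood model is close to unbiased when stopping depends only on observed HRCT scores. The inputs to the sizes above are all assumed. All of this stands, and it makes the concern conditional. It does not remove it: the article does not say which scans are used, does not settle the day-4 scan for a patient negative that day, and gives more than one rule for when assessment ends.

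A reader might infer two stronger points that the document does not support. One is that the planned analysis is biased. That would require later scans to enter the model, treatment to change clearance, and clearance to be tied to the HRCT course in a way the model misses; the article fixes none of these. The other is that the day-0 score goes unused. The article names a model and is silent on covariates; day 0 could be a covariate or the first repeated value, and an analysis plan or full protocol, not shown here, is where covariates are commonly listed. Omitting it from a randomised comparison would cost precision without causing bias.

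**Conclusion.** The point holds as an inconsistency in a primary endpoint with a conditional risk of bias. Timepoint, model and scan schedule do not define one analysis, and scans after day 4 are missing according to another primary outcome. If they are used and the conditions above are met, the comparison is typically shifted against the faster-clearing arm: under the assumed values by roughly a tenth of a point to about 0.4 at day 8, and by about 0.3 to 0.8 at day 12, for the likelihood models showing a material shift, on a 0–25 scale. Direction and conditions carry over to the trial; the sizes need not. The day-4 comparison is unaffected if the scan is taken regardless of that day's PCR. Adjusting for day 0 is a recommendation for precision or power.

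**What to change.** - Reconcile Table 1 with sections {12}, {18a} and {18b} on the HRCT timepoint and on what ends scanning and follow-up.
- Name day 4 as the only HRCT timepoint tested, as Table 1 already does.
- State that the scheduled day-4 scan is obtained in every randomised patient whatever the day-4 PCR result. Withdrawals stay with the missing-data methods in {20c}.
- Replace the mixed model by a single-timepoint ordinal model, or ANCOVA, with the day-0 score as covariate.
- Report day-8 and day-12 scans descriptively, stating that they come only from patients still PCR-positive when scanning was continued.

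The cost is wording in Table 1 and a clause in {12}. No new visit is needed; a scan is added only if the present clause was meant to cancel the day-4 scan on a negative result. The real downside is that later scans no longer contribute to the primary HRCT test.

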**Secondary outcomes**			
Mortality	Lower	Yes/No	Fisher exact test

### Interim analyses {21b}

The risk aptitude for this study is customized as low risk, considering the use of nutraceutical product. However, as it involves vulnerable COVID-19 patients and novel drugs are being tested for repurposing, strict safety measurements will be taken. As a part of our safety measurements, the investigator, [name] (Professor of Cardiology, SZH, Lahore), with the biostatistician, [name]. [name] (Dean faculty of biostatistics, UVAS, Lahore), will conduct an interim analysis. The prime focus of this analysis will be mortality and incidence of any serious adverse effects. This will be carried out after randomization and inclusion of half of the patients. For these specific outcomes, those conducting the interim analysis will be unblinded. No stopping rules for the primary endpoint have been defined as this is the first trial of its kind.

### Methods for additional analyses (e.g. subgroup analyses) {20b}

Adjusted and subgroup analysis may be applied as per the biostatistician, if needed. In that case, both unadjusted and adjusted analyses are provided along with the main analysis.

### Methods in analysis to handle protocol non-adherence and any statistical methods to handle missing data {20c}

The intention-to-treat analysis set will be used to test the superiority. All patients will be considered as randomized despite receiving the randomized treatment as per our anticipation. Reasons for each group’s randomization and withdrawal will be reported and compared qualitatively and sensitivity analysis (augmented data) is being used to overcome the effect of any missing data on results. The participants who withdraw consent for continued follow-up (Dropouts) will be assessed by modern imputation methods for missing data

### Plans to give access to the full protocol, participant-level data, and statistical code {31c}

Only the principal investigators will have access to the full trial dataset to ensure that the overall results are not disclosed by an individual of trial prior to the main publication. Grant public access to the full protocol, participant-level dataset, and statistical code will be given through publication.

## Oversight and monitoring

### Composition of the coordinating center and trial steering committee {5d}

Coordinating center and trial steering committee will be comprised of medical lab technologist ([name]), clinical pharmacist ([name]), clinical pharmacologists and toxicologist ([name]), virologist ([name]), immunologist ([name]), biostatisticians ([name]), epidemiologist ([name]), and consultants of medicine ([name], MBBS), pulmonology ([name]), and cardiologist ([name]). This committee will be responsible for the safety, trial safety, and dosage calculation to get results of endpoints. This will have all the authority to stop the clinical trial all together. Data management team will be comprised of principal investigators, co-investigators, and site investigators. This team will be responsible to ensure the execution of the clinical trial in best possible way as defined by the study protocol. Site investigators are responsible for data collection and quality check of data at collection points/ study setting. [name] will manage data compilation, cleaning, editing, and entry on SAS along with a biostatistician.

### Composition of the data monitoring committee, its role and reporting structure {21a}

Data monitoring committee (DMC) has a biostatistician ([name]), an epidemiologist ([name]), a microbiologist ([name]), a pulmonologist ([name]), and principal investigators ([name] and [name]) in it. There is no financial or non-financial conflict of interest as the committee will be independent of sponsor and competing interests.

### Adverse event reporting and harms {22}

The researchers will record any adverse, unpredictable, or undesirable sign and symptom and it will be discussed with the care providers. A comprehensive evaluation will be conducted to evaluate the co-relation between experimental drug and the developing signs and symptoms. The investigator will respond appropriately to ensure the wellbeing of the patient in case of any unforeseen event and all the details will be written carefully. Moreover, regular follow-up will be made certain until the patient regains his/her health. If the adverse event happens during the study intervention will be reported Institutional Review Board (IRB).

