### Intervention description {11a}

In this multi-armed study, ionic-iodine polymer complex will be given using three formulations with 200 mg of elemental iodine to evaluate efficacy for a maximum of 14 days or when the patient is fully recovered.
Arm A will be receiving 200 mg iodine complex capsule three times a dayArm B will be receiving iodine complex suspension syrup form 40 ml three times a dayArm C will be receiving iodine complex nasal spray 2 puffs three times a day.Arm X will be receiving a placebo of empty capsule three times a day.

All patients will receive standard care as per version 3.0 of clinical management guidelines for COVID-19 established by the Ministry of National Health Services of Pakistan COVID-19 guidelines of the study setting.

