### Criteria for discontinuing or modifying allocated interventions {11b}

Fixed doses will be given throughout the study and interventional drug administration will be stopped immediately in following conditions.
Patient becomes severely symptomatic during trial conduction.Any adverse drug reaction.Organ failure secondary to any administered drug.Denies/backs off from further participation.

Regardless of any of these conditions, the participant’s data will be retained and analyzed in the trial to follow-up and prevent any loss of data.

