### Provisions for post-trial care {30}

No post-trial care will be needed in our study setup as half-lives of the administered drugs are within hours to days.

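### Adverse-event ascertainment ends at a time set by recovery or PCR clearance, both primary outcomes; only death has a fixed 30-day window

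*Protocol article*

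**What the plan says.** All references are to the protocol article.

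- **Reporting.** Adverse event reporting and harms {22} gives one time condition for notifying the ethics board: "If the adverse event happens during the study intervention will be reported Institutional Review Board (IRB".
- **Recording.** The same section opens more broadly: "The researchers will record any adverse, unpredictable, or undesirable sign and symptom and it will be discussed with the care providers". It adds that "regular follow-up will be made certain until the patient regains his/her health". Neither sentence names a day.
- **Length of treatment.** Intervention description {11a} gives the drug "to evaluate efficacy for a maximum of 14 days or when the patient is fully recovered". Section {11b} also stops it for severe symptoms, any adverse drug reaction, drug-related organ failure or withdrawal, and keeps the participant's data in the analysis.
- **Data collection.** Section {18b} runs the study for each hospitalised or home-quarantined patient until two consecutive swabs are negative. It says that everything except 30-day mortality is collected during the hospital admission. For the period afterwards it says: "Follow-up will be done using phone numbers of the patients to access the mortality benefit of intervention".
- **Death.** Section {18a} counts deaths 30 days after randomisation in all groups.
- **After the trial.** Section {30} says: "No post-trial care will be needed in our study setup as half-lives of the administered drugs are within hours to days".

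**The concern.** Time to alleviation of symptoms and time to RT-PCR clearance are primary outcomes (Outcomes {12}, Table 1). The iodine arms are expected to improve both. If the period in which harms are captured ends when one of these outcomes occurs, an arm that improves faster is watched for less time. A crude comparison of the proportion of patients with an adverse event could then favour iodine when the drugs carry the same daily risk.

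The protocol gives this comparison some weight. The Discussion expects the trial to inform on efficacy and toxicity, and undertakes to look for nasal and mucociliary damage. The interim analysis {21b} centres on mortality and serious adverse effects. Death has a common 30-day window; no other harm does.

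**Working it through.** **No figure to reproduce.** The protocol gives no adverse-event rate, recovery time or window length in days. The check is a reading of the text, followed by an illustration on labelled assumptions.

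**Step 1: where each route ends.**

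| Route | Stated end | What sets it |
|---|---|---|
| Ethics-board reporting {22} with {11a} | full recovery, at most day 14 | primary outcome (symptoms) |
| The same, with {11b} | severe symptoms, reaction, organ failure, withdrawal | post-randomisation events |
| Recording {22} with {18b}, admission | discharge | clinical course |
| Recording {22} with {18b}, study conduct | second consecutive negative swab | primary outcome (RT-PCR) |
| Death {18a} | 30 days after randomisation | fixed, same in all arms |

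Every route except death ends at an event that treatment may influence. For a home-quarantined patient the admission rule gives no usable end date.

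**Step 2: days without stated adverse-event collection.** Dosing ends by day 14, counting from randomisation, so the gap to day 30 is at least 30 - 14 = 16 days. Swabs are taken every fourth day, so the earliest pair of consecutive negatives after baseline is days 4 and 8. Study conduct on the swab rule then ends no earlier than day 8, leaving at most 30 - 8 = 22 days. Some of the 16 days may still be covered if the patient remains in hospital or under swab follow-up.

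**Step 3: how far unequal windows could distort a crude proportion.** This uses the reporting route, where the window closes at recovery or day 14.

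Assumptions, none in the documents: exponential time to recovery with median m, so L = ln 2 / m; the same constant adverse-event hazard h in both arms; and 14-day risk q of 10% or 30%, so h = -ln(1 - q)/14, which is 0.00753 or 0.02548 per day.

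Mean window = (1 - exp(-14L))/L.

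- m = 10: L = 0.0693, mean 8.96 days
- m = 8: L = 0.0866, mean 8.11 days (ratio to m = 10: 0.91)
- m = 5: L = 0.1386, mean 6.18 days (ratio to m = 10: 0.69)

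Proportion with an event inside the window = h/(h + L) × (1 - exp(-14(h + L))).

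| Median recovery, placebo against iodine | q = 10% | q = 30% |
|---|---|---|
| 10 against 10 days | 6.45% against 6.45% | 19.75% against 19.75% |
| 10 against 8 days | 6.45% against 5.85% | 19.75% against 17.99% |
| 10 against 5 days | 6.45% against 4.48% | 19.75% against 13.96% |

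With no true difference in hazard, the apparent advantage runs from zero (equal recovery), through 0.6 to 1.8 points (10 against 8 days), to 2.0 to 5.8 points (10 against 5 days). A common fixed window makes the window ratio 1.00 by construction, apart from deaths and losses.

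**The case against.** The strongest reply is that reporting is not recording. The sentence with the time condition governs letters to the ethics board, does not contain the word only, and is loosely enough built to be read as covering the whole study. A safety comparison would use recorded events, which {22} leaves without a time limit. Patients are assessed daily, data are kept after a stop, and follow-up continues until health is regained. Table 1 plans no between-arm adverse-event test, and a condensed article may leave harm windows to the full protocol.

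Much of this stands. It rules out several stronger readings that a reader might infer:

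- **That harms count only while on drug.** The recording sentence says otherwise.
- **That a patient stopped for a reaction drops out of view.** The reaction arises on treatment and is reportable, and {11b} retains the data. What can fall outside the reporting rule is a new event after the stop.
- **That a patient who recovers on day 4 has 26 days of death-only follow-up.** Swab follow-up runs to day 8 at the earliest.
- **That the window closes before drug effects end.** Half-lives of hours to days mean that some exposure outlasts dosing, but no passage states how long effects last. {11b} names "Organ failure secondary to any administered drug" as a reason to stop, which half-life alone would not time, but this fixes no duration either.
- **That the telephone call asks about nothing but death.** {18b} states the call's purpose, not its script.

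The reply does not answer {18b}. That section states a limit on collection rather than omitting one, and its end points also depend on outcome. The open-ended promise in {22} and the admission limit in {18b} cannot both be followed as written.

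**Conclusion.** The point holds as one of unequal and unreconciled windows. Followed as written, ascertainment of every harm except death ends at recovery, day 14, an early stop, discharge or a second negative swab. No length is common to the arms.

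The direction of any distortion is not guaranteed. Faster recovery on iodine would shorten its window and could flatter it. Stops for reactions would shorten the window in whichever arm has more of them, and stops for severe symptoms would do so in the arm doing worse.

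The size rests wholly on the assumed recovery times, equal constant hazards and 14-day risks in the working, and on a crude comparison of proportions that Table 1 does not list. The illustration shows a possible distortion of a few percentage points, not an expected one. It is a cheap improvement to safety ascertainment and does not touch the sample size, alpha or power.

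**What to change.** In {18b} and {22}, state one window for both recording adverse events and reporting them to the ethics board, the same in all four arms: from first dose to day 30 after randomisation, whether or not the patient has recovered, been discharged or stopped study drug. In {18b}, exempt adverse events as well as mortality from the admission-only rule, and add adverse-event questions to the telephone contact already planned. State that the window also applies to home-quarantined patients.

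Sections {30}, {18b} and {22} must be reconciled on what follow-up takes place after the intervention ends. The choice of clinical provision is for the investigators.

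The cost is a wording change, a few more questions per call and slightly more reported events. Treatment is unchanged. Events reported by telephone will be less precisely characterised than those seen in hospital, but equally so in every arm if the same questions are asked blind to allocation.
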